#### Concealment mechanism {16b}

The allocation order is implemented and concealed by the randomization tool “randomizer” (randomizer.org; last access 8/15/2023). The allocation sequence is stored in a password-protected folder.

#### Implementation {16c}

Sealed envelopes are used to store the randomization result for the individual participant. These are opened only immediately before the intervention by the investigator.

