### Trial design {8}

We are planning an interventional, monocentric, randomized, controlled trial with two MDD patient groups of 30 participants each.

Our study is of the parallel group type, i.e., we are looking at two groups of patients in parallel, with one group of patients receiving an intervention while the other one does not. The framework is “superiority”: we expect to see superiority in outcome parameters in the intervention group. The allocation ratio in the intervention versus the control group is 30:30.

As it is to be expected that about 10% of the data will be lost due to the complex study protocol with several examinations at a total of four time points, at least 35 patients should be recruited per group. This minimum recruitment number seems achievable based on our experience with previous studies. The details of the intervention are outlined below.

In addition, an age-, sex-, and education-matched control group of 30 participants will be recruited, who will serve as a control only for the additional experimental investigations, which is the MRI part and the eyeblink conditioning. In these two subprojects, the first step is to evaluate the changes in the context of depressive illness in general compared to a healthy control group, see the “Outcomes {12}” section.

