### Who will take informed consent? {26a}

During outpatient or inpatient treatment, potential study patients receive information about the possibility of participating in the study and are asked for permission to contact them by telephone if they are interested. In addition, interested patients who have learned about the study via the LVR-University-Hospital homepage or have received the flyer about the study via psychiatrists in a private practice can contact us via an e-mail address set up specifically for the study.

In the next step, potential participants receive further relevant information such as the time of participation and duration of the examinations via telephone. In this process, the inclusion and exclusion criteria are also systematically checked. If there are no contraindications up to this point, an appointment is made to see the investigator for an in-depth educational interview, and verbal as well as written informed consent to participate in the study is obtained.

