### Assignment of interventions: allocation

#### Sequence generation {16a}

The participants are divided into two groups (intervention group versus control group) with an allocation ratio of 1:1 and *n* = 30 participants per group. Stratification by gender is performed to ensure a balanced gender ratio; beyond that, there are no other factors used for stratification. The freely available online software “randomizer” (randomizer.org; last access 8/15/2023) will be used for this purpose.

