### Assignment of interventions: blinding

#### Who will be blinded {17a}

This is a double-blinded study, i.e., the participants do not know which group they were assigned to, nor that an intervention takes place during the educational process. Since the investigator performs the medical consultation, which at the same time is the intervention, blinding is not possible here. The additional scientific staff who survey the outcomes (i.e., eyeblink conditioning and cognitive tasks) are blinded regarding the intervention group during the entire course of the study. As the therapist factor should not be underestimated, the protocol is realized in a way that all the patients interact with the same therapist for each respective procedure (the same person performing the psychological tests and interviews, the same person applying the TMS treatment, and the same person communicating regarding the informed consent).

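### The unblinded investigator who takes consent and delivers every consultation also opens the envelopes, so under a 30:30 gender-stratified scheme the next allocation can be guessed somewhat better than chance

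*Protocol article*

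**What the plan says.** All references are to the protocol article.

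- **Entry.** Under Who will take informed consent? {26a}, after a telephone check of the criteria, "an appointment is made to see the investigator for an in-depth educational interview", and consent to the study is obtained there. The section on the coordinating center {5d} says that the clinic physician who runs the study day to day obtains consent.
- **Delivery.** Who will be blinded {17a}: "Since the investigator performs the medical consultation, which at the same time is the intervention, blinding is not possible here". The same section has one person conduct the informed-consent communication for all patients, to hold the therapist factor constant.
- **Allocation.** Trial design {8}: "The allocation ratio in the intervention versus the control group is 30:30". Sequence generation {16a} repeats 1:1 with 30 per group and adds: "Stratification by gender is performed to ensure a balanced gender ratio; beyond that, there are no other factors used for stratification".
- **Concealment.** Concealment mechanism {16b}: "The allocation sequence is stored in a password-protected folder". Implementation {16c}: "Sealed envelopes are used to store the randomization result for the individual participant", and "These are opened only immediately before the intervention by the investigator".

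Trial design {8} and Sample size {14} also call for at least 35 recruits per group to cover about 10% loss.

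**The concern.** Concealment has two parts. The current assignment must be hidden until the patient is irrevocably entered, and the next one must not be predictable by whoever controls entry. Opening a sealed envelope just before the consultation serves the first part. The second is weakened because the person at the point of entry has opened every earlier envelope and knows the running count in each gender. When group totals are restricted, that count carries information about what comes next.

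There is some room to act on a guess. Several entry criteria in {10} call for judgement (general condition, relevance of comorbidities), and the Discussion allows the pre-treatment examinations to be spread over several appointments, so timing is flexible. The team expects superiority of the enhanced consultation ({8}). If patients with a better outlook were entered when that arm seemed due, the groups would differ before treatment. Blinding of patients and raters acts only after entry and would not undo this. With about 30 per arm such a difference would be hard to see in a baseline table.

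**Working it through.** **The plan's own figures.** The article gives no figure for predictability. Its recruitment target is consistent with its loss rate: 30 / (1 − 0.10) = 33.3, rounded up to 34, which at least 35 covers.

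**Inputs from the article.** 1:1 allocation and 30 per group ({8}, {16a}); gender as the only stratum ({16a}); past allocations known to the person who consents and delivers ({16c}, {17a}, {26a}, {5d}).

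**Assumptions.** List length, stratum sizes and any blocking are not stated. I take closed lists whose structure the guesser knows, and vary them.

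**Formula.** The guesser names the arm that is behind and picks either arm when they are level (the Blackwell–Hodges convergence strategy). For a closed list with m per arm, the expected number of correct guesses above one half is

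E(m) = (4^m / C(2m, m) − 1) / 2.

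**Results.**

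- One list, m = 30: 4^30 / C(60, 30) = 9.749, so E = 4.37. Correct guesses: (30 + 4.37) / 60 = 57.3%.
- Two gender lists, m = 15 each: 4^15 / C(30, 15) = 6.922, so E = 2.96 per list and 5.92 in all. Correct guesses: (30 + 5.92) / 60 = 59.9%.
- Uneven genders (20:20 and 10:10): 59.7%.
- Lists for 35 per group (18:18 and 17:17): 41.47 / 70 = 59.2%.

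On the stated scheme the gain is thus about 7 to 10 percentage points, or roughly 4 to 6 extra correct guesses in 60. Recruiting 35 instead of 30 per group hardly changes it.

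**Assignments known with certainty**, if the end of a list is known: 2m / (m + 1) per list. This gives 60/31 = 1.9 for one list and 2 × 30/16 = 3.75 for two, all at the end of a list.

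**Sensitivity to an unstated feature.** With blocks of 4, E(2) = (16/6 − 1) / 2 = 0.833 per block. Over 15 blocks that is 12.5, or 42.5 / 60 = 70.8%. The article mentions no blocks, so this only shows what the revised wording should rule out.

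**From guessing to bias (illustration only).** If every entry were shifted in prognosis by η SD toward the guess, the expected difference between arms would be 2ηE / 30. For two 15:15 lists this is 0.10 SD at η = 0.25 and 0.20 SD at η = 0.5. For one 30:30 list it is 0.07 and 0.15 SD. Nothing in the article gives a value for η.

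**The case against.** Concealment is described: a randomization tool, a protected file, and individual sealed envelopes opened at the last moment. Many criteria are firm (age, depression severity by scale and structured interview, two failed antidepressants, TMS contraindications, earlier TMS). Using one communicator is a deliberate control. Custody of the list and block structure are details that a journal article may leave to the full protocol. All of this stands, and for that reason the missing name of a list-holder is not the point. The point is that the article assigns the opening of envelopes to the person who also consents and delivers.

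Four stronger readings are tempting, and the article does not support them.

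- *The same physician also screens.* {26a} does not say who makes the telephone check. The consent interview alone places the investigator at the point of entry.
- *The next allocation is effectively known, and the last ones are certain.* Certainty needs a known list end. No list length is given, the gender mix is not fixed in advance, and at least 35 per group are to be recruited. Rates near 71% need small blocks that no section mentions.
- *Type I error is inflated by a stated amount.* The 0.10 to 0.20 SD above would raise a 5% test to about 7% to 12%, but only for one unpaired comparison with every entry steered. The main planned analysis in {20a} is a repeated-measures ANOVA, and T1 is one of its four time points. A constant difference already present at T1 would not create a group-by-time interaction; steering on later course could.
- *Patients who doubt the study can be diverted at will.* The passage on alternative treatments in {11c} concerns candidates who themselves doubt that they can attend the visits. It does not describe a screen on prognosis.

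**Conclusion.** The point holds in a limited form. The article itself fixes the overlap of roles, and with it the allocation can be predicted better than chance: about 57% for one closed 30:30 list and about 60% for two closed 15:15 gender lists, against 50%. These rates assume closed lists with a structure known to the guesser. They are insensitive to the gender mix and to 30 or 35 per group, and would rise materially only under small blocks. The consequence is an avoidable opening for selective entry or timing by arm. Whether any bias follows, and how much, depends on steering that the article gives no reason to think takes place. It is worth closing because Sample size {14} and the Discussion expect the effect to be smaller than in the study used for planning, and because the remedy costs little.

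**What to change.** Revise {16b} and {16c} to state:

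1. A colleague not involved in recruitment generates and holds the lists. The consenting physician has no access to the folder or to unopened envelopes.
2. Eligibility, consent and T1 are completed and recorded with date before allocation.
3. Only then does the list-holder release that participant's allocation, immediately before the consultation.
4. Per-gender lists are generated longer than needed, without small fixed blocks, and their structure is unknown to the consenting physician.

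The cost is a little coordination by existing staff, an amendment notified as {25} provides, and a final split that may differ from 30:30 by a few patients. One communicator for all patients can be kept. The participant timeline is a figure that I could not see. If T1 already precedes the consultation, item 2 changes only the record; any questionnaire meant to register the consultation's effect on expectation would stay after it.

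Trial status gives November 2023 as the goal for completing recruitment. If entry has closed, the report should state who held the list, how it was structured, and the order and dates of consent and allocation.

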### Assignment of interventions: blinding

#### Who will be blinded {17a}

This is a double-blinded study, i.e., the participants do not know which group they were assigned to, nor that an intervention takes place during the educational process. Since the investigator performs the medical consultation, which at the same time is the intervention, blinding is not possible here. The additional scientific staff who survey the outcomes (i.e., eyeblink conditioning and cognitive tasks) are blinded regarding the intervention group during the entire course of the study. As the therapist factor should not be underestimated, the protocol is realized in a way that all the patients interact with the same therapist for each respective procedure (the same person performing the psychological tests and interviews, the same person applying the TMS treatment, and the same person communicating regarding the informed consent).

#### Procedure for unblinding if needed {17b}

Since the intervention is not an alternative treatment, there are no conceivable reasons that would necessitate unblinding.

### Data collection and management

#### Plans for assessment and collection of outcomes {18a}

A description of the study instruments including corresponding references can be found in the “Outcomes {12}” section. All the staff involved in the data collection will be trained accordingly prior to the start of the study; furthermore, the first investigations performed by staff will take place under the supervision of the principal investigators.

#### Plans to promote participant retention and complete follow-up {18b}

The participants are informed that another detailed test will take place at the time point T4 after the treatment; if desired, they will be informed about the point values of the questionnaires. Furthermore, there is a genuine motivation of the participants to receive the treatment at a sufficient length. In case of discontinuation or deviation from the study protocol, the reason(s) for discontinuation will be recorded and the tests that would have been scheduled at T4 will take place at this time.

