Today, the topic of treatment expectation may be of particularly great relevance, as patient-physician communication has taken a back seat in the clinical setting in the face of numerous bureaucratic and economic challenges. New insights into the impact of treatment expectations could drive significant change, for example, regarding the design of the patient education discussion.

Transcranial magnetic stimulation (TMS) therapy is approved for the treatment of depressed patients who did not sufficiently benefit from standard antidepressant pharmacotherapy; its effectiveness has been shown in several meta-analyses [8]. The stimulation site of TMS treatment is the left dorsolateral prefrontal cortex. It is usually applied for a duration of 4 to 8 weeks, 5 days a week for 30 min [8, 9]. To date, it remains unclear how exactly TMS exerts its effects. Resting-state (rs) functional imaging studies found characteristic alterations in MDD which can be influenced by TMS [10]. In MDD, a hyperconnectivity within the frontoparietal network (involving the dorsolateral prefrontal cortex and the posterior parietal cortex) and a hyperconnectivity within the default mode network (DMN, involving the prefrontal and cingulate cortex) have been reported [10]. After repetitive (r)TMS treatment, Philip and colleagues [11] found altered rs functional connectivity between the prefrontal cortex and the subgenual anterior cingulate cortex. Higher connectivity within the DMN seems to predict the beneficial effects of both pharmacotherapy and TMS.

Interestingly, these same networks are implicated in expectation effects: Burke and colleagues [12] conducted a meta-analysis on neuroimaging studies of placebo effects and compared clusters of activation (and deactivation) with TMS and deep brain stimulation (DBS) targets for depression treatment and found an extensive overlap. This raises both the question and the hypothesis: can we assume a bilateral interaction between placebo mechanisms and TMS?

Another interpretation of this observation could be that there seems to be an overlap of the underlying cognitive-affective and reward-based substrates in MDD and placebo effects [12].

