#### Criteria for discontinuing or modifying allocated interventions {11b}

Overall, the study is at a very low risk for potential harm. No harm is expected from the intervention in the form of modified patient education about the approved therapy with TMS. Prior to the start of the study, study participants will be asked to indicate whether they would like to be informed of incidental findings in addition to this education.

The discontinuation criteria for individual participants are the occurrence of intolerable and/or unexpected undesirable side effects during the therapy with TMS, the occurrence of the exclusion criteria during the course of the therapy, violation of the study protocol, and other circumstances that would endanger the health of the participant if he or she continued to participate in the study, as well as on participant request. Change of medication during the treatment is not an exclusion criterion per se but will be recorded as an event that will need additional control.

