#### Relevant concomitant care permitted or prohibited during the trial {11d}

The aim is to ensure that during study participation, any existing drug and/or psychotherapeutic treatment is continued with as little change as possible. In the event of a relevant change during study participation, discontinuation must be discussed individually. Change of medication during the treatment is also not an exclusion criterion per se but will be recorded as an event that will need additional control.

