### Outcomes {12}

#### Primary outcomes

Psychometric tests to assess therapy success: The tests will be administered at four points in time (T1: before therapy, T2: in week 2 of therapy, T3: in week 3 of therapy, T4: after therapy). T1 was defined as the examination within a period of 2 weeks before the start of therapy, and T4 as the examination within a period of 2 weeks after the end of therapy.

The following tests are used, some of which are questionnaires to be completed by the patient and some of which record the clinical examiner’s impression.

Beck Depression Inventory-II (BDI-II): This instrument measures the severity of depressive symptoms. In the form of a questionnaire, the patient self-reports how pronounced certain symptoms were during the previous week [27].

Montgomery Asberg Depression Scale [MADRS [28]]: In contrast to the BDI-II, MADRS is an instrument for third-party assessment of the severity of a depressive episode. The questionnaire is completed by the patient’s clinical practitioner as part of the usual clinical routine or by a clinical psychologist, who is blinded to intervention allocation.

Clinical Global Impression severity scale (CGI): This is a brief third-party assessment of the severity of illness by the examiner [29, 30], who is blinded to intervention allocation.

Snaith-Hamilton Pleasure Scale: This questionnaire is used to measure subjectively experienced joylessness (anhedonia) in psychiatric patients [31, 32].

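### The T4 tests are moved to the time of stopping or deviating, with no later assessment at the planned time, so T4 mixes full-course with part-course values

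*Protocol article*

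**What the plan says.** Section {18b} of the protocol article sets the rule. Two kinds of event trigger it, a stop or a departure from the protocol, and the reasons are noted. For either event the section then fixes the timing of the final battery: "the tests that would have been scheduled at T4 will take place at this time". No second assessment at the planned time is described.

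The primary outcomes (section {12}) are four depression scales read at four times: "T1: before therapy, T2: in week 2 of therapy, T3: in week 3 of therapy, T4: after therapy". The last is defined as "T4 as the examination within a period of 2 weeks after the end of therapy". The background (section {6a}) says of TMS: "It is usually applied for a duration of 4 to 8 weeks, 5 days a week for 30 min". The article does not fix the course length for this trial more closely.

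The grounds for stopping in section {11b} include "the occurrence of intolerable and/or unexpected undesirable side effects during the therapy with TMS", protocol violation and the participant's own request. For changes in concomitant treatment, section {11d} says: "In the event of a relevant change during study participation, discontinuation must be discussed individually".

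Sections {20a} and {20c} plan a repeated-measures ANOVA, t-tests or chi-square tests at single time points, and a linear mixed model if values are missing.

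**The concern.** Section {18b} is a rule about when data are collected. It ties the final measurement to each patient's own course. Someone who stops in week 1, 2 or 3 has the T4 battery before, or at about the same time as, T2 or T3. The same battery in a completer falls after the whole course. If both are entered as T4, the time-point comparison and the group-by-time analysis set unlike measurements side by side.

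The reasons for stopping can be related to outcome. The intervention is meant to raise expectations of the same daily TMS treatment that both arms receive, and section {11c} calls adherence a major challenge. Persistence could therefore differ between arms. If it did, part of the T4 difference would reflect when patients were measured and not how they fared over a common period.

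An analysis plan could re-date the early values. It could not recover a scheduled T4 that was never taken.

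**Working it through.** **The plan's own figure on loss.** Section {14} starts from 30 per group and expects about 10% of data to be lost: 30 / (1 − 0.10) = 33.3, so 34. The article asks for at least 35, which is consistent. If the 10% were all early stoppers, it would concern 0.10 × 70 = 7 patients.

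**Timing, side by side.** T2 and T3 fall in weeks 2 and 3, and a usual course is 4 to 8 weeks. A stop at week 2 therefore falls after 2/8 = 25% to 2/4 = 50% of the course. For a deviator who remains on TMS, testing at the time of deviation cannot also fall after the end of therapy, so {18b} and {12} conflict for that patient.

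**Size of the shift.** The following are assumptions, not document figures: full-course gain G of 1.0 to 1.5 SD, linear in time; course length L = 6 weeks; stop at w = 2 weeks; stopping share 5% in the intervention arm and 15 or 20% in the control arm; no true group effect.

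Shift = (p_control − p_intervention) × G × (1 − w/L), with 1 − 2/6 = 0.667.

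| Stopping | G = 1.0 SD | G = 1.5 SD |
|---|---|---|
| 5% vs 15% | 0.10 × 1.0 × 0.667 = 0.07 | 0.10 × 1.5 × 0.667 = 0.10 |
| 5% vs 20% | 0.15 × 1.0 × 0.667 = 0.10 | 0.15 × 1.5 × 0.667 = 0.15 |

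With L = 4 weeks the range is 0.10 × 1.0 × 0.50 = 0.05 to 0.15 × 1.5 × 0.50 = 0.11 SD. With L = 8 weeks it is 0.10 × 1.0 × 0.75 = 0.08 to 0.15 × 1.5 × 0.75 = 0.17 SD. If the intervention arm stops more often, the sign reverses.

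**What is strictly due to timing.** The formula charges each stopper with the whole remaining treated gain. If only a share k of that gain would have occurred off TMS by the planned T4 date, the shift is multiplied by k. At k = 0.5 the 6-week range becomes about 0.03 to 0.08 SD, and at k = 0 it vanishes. For a deviator who continues TMS, k is close to 1.

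**Consequence for a t-test at T4.** With 35 per arm and unit SD, SE = √(2/35) = 0.239 SD. The two-sided 5% rejection rate with no true effect is 1 − Φ(1.96 − b/SE) + Φ(−1.96 − b/SE). A shift b of 0.10 SD gives 7.0%, and 0.15 SD gives 9.6%.

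**Equal stopping.** With 10% stopping early in each arm, at the same time and for the same reasons, the net shift is 0. A true effect of 0.40 SD (also assumed) that builds up linearly would be read as 0.40 × (1 − 0.10 × 0.667) = 0.37 SD. This is dilution only.

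**The case against.** An assessment at stopping is good practice. For a patient who stops TMS, therapy has ended, so testing then fits the T4 definition literally. The article also does not say that the early result is analysed as T4, and coding of early visits is often left to an analysis plan. Section {11b} lists protocol violation among the discontinuation criteria, so the authors may have had only patients who leave treatment in mind when they wrote deviation. These points are fair. They make the labelling an inference and the deviator case a matter of wording. They do not supply the missing later assessment.

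A reader might go further in four ways that the text does not support:

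- **The mixed model would see nothing missing.** A patient who stops in week 2 and leaves has no T3, so the mixed model could be triggered. If the early value is coded as T4, the model would still take it as an observed T4.
- **The rule is last observation carried forward.** It is not, because a new measurement is made at stopping and no older score is copied.
- **Stopping decisions are taken open-label.** Patients do not know that two consultation types exist, and MADRS and CGI raters are described as blinded. Only the consulting investigator is stated to be unblinded, and {11d} does not say who decides.
- **Medication change will be a covariate.** Section {11b} says only that a change "will be recorded as an event that will need additional control". That could mean monitoring or a sensitivity analysis, and {20a} names no covariate for the clinical outcomes.

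**Conclusion.** The point holds as a weakness in data collection that is cheap to repair. As written, {18b} replaces the scheduled final assessment with one at a time set by the patient's own course. Its wording also reaches patients still on TMS, which conflicts with {12}.

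A biased comparison does not follow automatically. It needs early stopping or deviation to differ by arm in frequency, timing or reason. The article gives grounds to think this possible and no evidence that it will happen. Under the 6-week assumptions above, the shift is at most about 0.07 to 0.15 SD, and less to the extent that stoppers would not have improved further off treatment. That is modest, but sections {14} and Discussion themselves anticipate an effect smaller than in the study used for planning. Any real effect of stopping treatment would remain after the fix and belongs in the comparison.

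**What to change.** Amend {18b} as follows:

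- Keep the assessment at stopping, but record it as a separate early-termination visit with its actual date, not as T4.
- Invite every randomised patient to T2, T3 and T4 at the originally scheduled times, whether or not TMS continued and whether or not they deviated, unless consent is withdrawn. Record the planned end-of-course date at the start of therapy so that the T4 window is fixed in advance.
- State in {20c} that all randomised patients are analysed as allocated, with the mixed model for values still missing.

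This changes measurement only and no treatment rule. The cost is a wording amendment and one or a few extra contacts for each patient who stops early. That is about 7 patients if the expected 10% loss is all early stopping.
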